### Data collection

The basic data are as follows: (1) demographic including gender, age, height, weight, waist circumference, hip circumference, body mass index and waist-to-hip ratio; (2) vital signs; (3) duration of diabetes; (4) other medical history and treatment history; (5) women of childbearing age should have a urine pregnancy test, and be inquired at each visit to record their menstrual history.

Blood and urine samples should be collected in the morning with an empty stomach for at least 8 h. The fasting serum samples for detection of TNF-α, IL-6, ROS, SOD and AGEs will be stored at -20 °C. It will be detected with enzyme-linked immunosorbent assay by an independent laboratory from JUJIN BIOTECHNOLOGY CORPORATION (Chengdu, China). The fasting plasma samples for detection of lipidomics will be stored at -80 °C. It will be detected with non-targeted lipidomics analysis platform based on Q Exactive (Thermo Scientific™) mass spectrometry system by Shanghai Lu Ming Biotech Co., Ltd. (Shanghai, China). Other outcomes will be measured by Hospital of Chengdu University of TCM on the same day.

### Drop-out criteria

Participants who have intolerable adverse reaction and withdraw voluntarily during the trial.The ratio of ALT to AST of participants is 3 times higher than the upper limit of normal value of that, and it is still abnormal after review within a week.Creatinine of participants is 1.5 times higher than the upper limit of normal value of that, and it is still abnormal after review within a week.Participants who fail to take the drugs as required or have incomplete data.Participants violate the protocol to change or add drugs that are not within the prescribed scope and affect the assessment of efficacy.Participants who are lost to follow-up without explanation.Participant who is unblinding.

They will be required to return for the last observation as much as possible, and the relevant data will be included in the datasets.

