### Exclusion criteria

Patients with calcified plaques or unstable plaques in lower extremity or carotid arteries, arterial stenosis (vascular inner diameter stenosis ≥ 50%), or arterial occlusion.Patients who have been diagnosed with coronary heart disease by coronary angiography, or whose electrocardiogram and clinical manifestations suggest coronary heart disease, or who have had cardiovascular and cerebrovascular events, such as acute coronary syndrome and cerebral infarction.ABI ≤ 0.9.Fasting TG > 5.7 mmol/L.Patients with abnormal liver and kidney function, such as the ratio of serum alanine aminotransferase (ALT) to aspartate aminotransferase (AST) 1.5 times higher than the upper limit of normal value of that, creatinine higher than the upper limit of normal value of that, estimated GFR ≤ 60 ml·min^−1^·(1.73m^2^)^−1^.Patients with acute metabolic disorders such as diabetic ketoacidosis, or severe stress, occurred within 1 month before screening.Patients with serious illnesses whose life expectancy does not exceed 2 years, or malignant tumor, or mental diseases.Patients who are known to be allergic to the ingredients in SQXT formula or its preparations.Having a history of alcoholism or drug abuse.Women who are preparing for pregnancy, or pregnant, or lactating women.

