#### Safety outcomes

Adverse event (AE) will be collected after the participants begin to receive drugs. The record of AE includes the following: descriptive analysis, time of occurrence and termination, severity, frequency of occurrence, whether treatment is needed, and if necessary, the treatment given needs recording.

Participants will be monitored for vital signs (body temperature, respiration, heart rate, BP) during the outpatient visit every 4 weeks, and will be asked for if they have any symptoms of discomfort.

Participants will have the following tests at the beginning and end of intervention: blood, urine and stool routine examination, electrocardiogram, liver function test (ALT, AST, TBIL, AKP, GGT), and renal function test (blood urea nitrogen, creatinine). Systemic symptoms of participants will be closely observed. If a participant has suspicious symptoms of respiratory system, circulatory system, liver or kidney disease, he will be immediately tested on safety.

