## Trial status

The recruitment of participants has started in June 2021 and is going.

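### The only laboratory liver withdrawal rule is set on the ALT-to-AST ratio, which stays flat when both enzymes rise together; it should be ALT or AST, each against its own upper limit

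*Protocol article*

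**What the plan says.** The Drop-out criteria contain one laboratory rule for the liver: "The ratio of ALT to AST of participants is 3 times higher than the upper limit of normal value of that", with the confirmation condition "and it is still abnormal after review within a week". The next item is the renal rule, "Creatinine of participants is 1.5 times higher than the upper limit of normal value of that", which compares one analyte with its own limit. The other items in that list are voluntary withdrawal for an adverse reaction that cannot be tolerated, poor adherence or incomplete data, prohibited medication, loss to follow-up and unblinding. None of these is a laboratory liver criterion.

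The Exclusion criteria rule out patients whose liver or kidney function is abnormal and give as the liver example "the ratio of serum alanine aminotransferase (ALT) to aspartate aminotransferase (AST) 1.5 times higher than the upper limit of normal value of that".

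The Safety outcomes section lists the enzymes as separate measurements, "liver function test (ALT, AST, TBIL, AKP, GGT", taken at the start and end of the intervention. A participant with suspicious symptoms in between "he will be immediately tested on safety". No section states a normal limit for an ALT-to-AST ratio, and none sets a threshold on ALT or AST separately.

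**The concern.** A liver stopping rule should respond to the size of an enzyme rise. The ratio of two enzymes responds to the balance between them. When ALT and AST rise in proportion, the ratio is the same at 10 times the limit as at normal values. When AST rises more than ALT, the ratio falls.

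If staff apply the rule as written, a participant taking the study granules could have marked hepatocellular injury and still not meet the only laboratory liver trigger for withdrawal. Coming off treatment would then depend on other routes, such as the participant choosing to stop because of an intolerable reaction.

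There is a smaller effect on the analysis. The Data analysis section leaves participants who drop out for any reason out of the per-protocol set, so a mis-stated withdrawal criterion can also change who is in that set.

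**Working it through.** **Inputs from the protocol**
- Multiple for withdrawal: k = 3 (Drop-out criteria).
- Multiple in the exclusion example: k = 1.5 (Exclusion criteria).

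**Assumptions, because the protocol gives no figures**
- Upper limit of normal of the ratio, U: 1.0, 1.5 or 2.0.
- R = ULN(ALT)/ULN(AST): 0.8, 1.0 or 1.5.

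**Formula.** Let ALT be a times its own limit and AST be b times its own limit. Then

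ALT/AST = (a/b) × R.

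The rule as written is met when (a/b) × R > k × U. The alternative rule is met when a > k or b > k. Only a/b enters the written rule. Multiplying both enzymes by any common factor leaves the ratio unchanged.

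**Withdrawal trigger.** 3U = 3.0, 4.5 or 6.0 for U = 1.0, 1.5 or 2.0.

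| Case | Ratio at R = 0.8 | R = 1.0 | R = 1.5 | Rule as written (3.0 to 6.0) | ALT or AST > 3 × own limit |
|---|---|---|---|---|---|
| a = 10, b = 10 | 0.8 | 1.0 | 1.5 | never met | met |
| a = 10, b = 5 | 1.6 | 2.0 | 3.0 | never exceeded (a tie at R = 1.5, U = 1.0) | met |
| a = 5, b = 10 | 0.4 | 0.5 | 0.75 | never met | met |
| a = 10, b = 3 | 2.67 | 3.33 | 5.0 | met in part of the range | met |

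The general condition is a/b > 3U/R. Over the assumed range this runs from 3.0/1.5 = 2.0 to 6.0/0.8 = 7.5. ALT must therefore exceed AST by that factor, in multiples of their own limits, however high either enzyme is.

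**The opposite error.** Take both limits as 40 U/L (R = 1.0), with ALT 40 and AST 13. Neither enzyme is above its limit, yet the ratio is 40/13 = 3.08. That exceeds the withdrawal trigger of 3.0 if U = 1.0. It also exceeds the exclusion example's threshold of 1.5U = 1.5, 2.25 or 3.0 at all three values of U. The reworded rules would not fire.

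**Exclusion example.** With a = b = 10, the ratio of 0.8 to 1.5 never exceeds 1.5U (1.5 to 3.0). With a = 10 and b = 5 at R = 1.0, the ratio of 2.0 exceeds it only if U = 1.0.

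**Reading the sections side by side.** The creatinine rule sits next to the liver rule, has the same form, and uses a single analyte against its own limit. The Safety outcomes section treats ALT and AST as separate tests. Both points suggest that the intended rule was ALT or AST, each against its own limit.

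**The case against.** The strongest reply is that this is a slip of translation, not a flawed rule. The neighbouring creatinine item and the separate listing of ALT and AST point to the intended meaning. The literal rule also cannot be applied without inventing a normal limit for the ratio, so staff may well be using the sensible reading already. Nothing in the article shows that they are using the literal one. This is fair, and it limits what can be said about actual harm. It does not make the text right: the same wording appears in two places and nothing in the article corrects it.

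Four narrower points also have some force.
- **Exclusion criteria.** The ratio is only an example under a general exclusion, so raised enzymes can already keep a patient out. This stands. The weight of the finding is on the Drop-out criteria, which have no such general wording.
- **Reach of the rule.** Liver tests are scheduled only at the start and end, so during treatment the rule acts only on symptom-prompted tests, when the participant is already under clinical attention. This stands. Symptomless injury could go unseen until week 12 under either wording, and rewording does not change that.
- **Selected cases.** Some uneven rises do trigger the written rule, as the 10-fold and 3-fold case shows. This stands, but it does not rescue the proportional and AST-dominant cases.
- **Inference.** Sample size, power, alpha and the primary outcome are untouched. This stands; the issue is participant safety.

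**Conclusion.** The concern holds. As written, the only laboratory liver withdrawal trigger does not measure the size of an enzyme rise. With the ratio's upper limit anywhere from 1.0 to 2.0 and ULN(ALT)/ULN(AST) from 0.8 to 1.5, both enzymes at 10 times their limits never meet it, and neither do ALT at 10 times with AST at 5 times. Read as ALT or AST above 3 times its own limit, the rule catches both. These limits are assumptions, but the failure under a proportional rise needs only a trigger above the ratio seen at normal values.

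This should be fixed. It is a stated safety threshold on the wrong quantity. Its seriousness is tempered by the likely intended meaning, the general wording of the exclusion criterion and the remaining clinical routes to withdrawal. Confidence in the textual error is high; whether it has affected any participant cannot be told from the article.

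**What to change.** - **Drop-out criteria:** replace the ratio with *ALT or AST above 3 times its own upper limit of normal*, keeping the existing one-week recheck.
- **Exclusion criteria:** as a conforming edit, make the example *ALT or AST above 1.5 times its own upper limit of normal*.
- **Multiples:** keep 3 and 1.5 unless the sponsor's clinicians choose otherwise.
- **Participants so far:** the Trial status section says "The recruitment of participants has started in June 2021 and is going". The sponsor should confirm which reading has been used for those already screened and treated.

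The cost is two phrases in a protocol amendment. ALT and AST are already measured, so no tests are added, and no change to the test schedule is requested.

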### Blinding

Investigators, participants, outcome assessors, and data analysts will be blinded. Outcome assessors will follow the standard operating procedure to complete tests. The third-party drug management staff from the Sichuan Province Evidence-based Medicine Center of TCM will blind investigational drugs according to random sequence, so that the drugs could not be distinguished according to their numbers. The drug management staff shall not directly participate.

The data analysts will be unblinded at the first level after the database is locked, and unblinded at the second level after statistical analysis is completed. In case of emergency such as serious adverse event and suspected unexpected serious adverse reaction, the participant’s allocated intervention will be revealed urgently, and investigator should treat he and record the time, date and reason of unblinding.

In order to ensure stability of the drugs, increase convenience of taking medicine, and remove the influence factors such as the method of decoction and the origin of medicinal materials, SQXT formula and placebo will be used in granules form. In accordance with the *Standard for the Use of Food Additives in the National Standard for Food Safety*, the placebo is made from maltodextrin and food additives such as food colorants and bitters. SQXT formula and placebo are similar in color, smell, taste, appearance, packaging, and tag. Both of them are produced by Sichuan Neo-Green Pharmaceutical Technology Development Co. Ltd. (Sichuan, China).

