#### Endpoint outcomes

The incidence of endpoint events and the time to progression to endpoint will be evaluated. Endpoints events include:The progression of peripheral artery disease is defined as bilateral carotid and lower extremity arteries stenosis or arterial occlusion.Major adverse cardiac events include cardiovascular death, non-fatal myocardial infarction, ischemic stroke, and hospitalization for heart failure.Diabetic foot ulcer.

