### Data analysis

The statistical analysis will be conducted by the third-party statistician from the Sichuan Province Evidence-based Medicine Center of TCM using Stata software (version 16.0). The statistical analysis plan is completed and confirmed before the start of trial.

The Full Analysis Set (FAS) includes participants who have been randomized to receive the drugs at least once. Missing data will be used the last observation carried forward (LOCF) method. The Per-protocol set (PPS) includes participants who follow the protocol to implement the inclusion and exclusion criteria and interventions, and complete all the visit plans. It does not include participants who drop-off, lost to follow-up, and discontinue medication for any reason. Only participant with an effective medication rate between 80 and 120% can be included in PPS analysis. The safety set (SS) includes participants who have been randomized to receive the drugs at least once and have experienced AE.

The descriptive statistics of enumeration data will be presented as frequency and percentage. Normally distributed variables will be presented as mean and standard deviation, and non-normally distributed variables will expressed by median and interquartile range. Difference between groups will be assessed with t-test, analysis of variance (ANOVA), rank sum test, and chi-square (χ2) test. Survival analysis will be used for comparison of endpoint outcome between groups, and Kaplan–Meier curve will be used to explore each possible relevant factor. The cox multiple regression model will be used to detect the influence of prognostic factors on endpoint outcome if the amount of data allows. AE will be analyzed and described in detail, and the χ2 test will be used to compare the differences between groups if necessary. The statistical significance is defined as *p* ≤ 0.05.

Subgroup analysis will be based on HbA1c. Level of HbA1c will be stratified into ≥ 8.0% and < 8.0% to evaluate correlation between glycemic control of diabetic patients with macroangiopathy and outcome indicators [37].

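### One drop-out status covers stopping drug, protocol deviation and leaving the study, and it does not secure the week-12 CIMT for participants who could still be followed

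*Protocol article*

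**What the plan says.** All places are in the protocol article.

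- **Drop-out criteria.** One list holds intolerable reactions with voluntary withdrawal, laboratory thresholds, disallowed medication changes, unexplained loss to follow-up, "Participants who fail to take the drugs as required or have incomplete data" and "Participant who is unblinding". For everyone on it: "They will be required to return for the last observation as much as possible, and the relevant data will be included in the datasets".
- **Blinding.** "In case of emergency such as serious adverse event and suspected unexpected serious adverse reaction, the participant’s allocated intervention will be revealed urgently".
- **Endpoint outcomes.** "The incidence of endpoint events and the time to progression to endpoint will be evaluated". Among these events: "Major adverse cardiac events include cardiovascular death, non-fatal myocardial infarction, ischemic stroke, and hospitalization for heart failure".
- **Outcome measurement.** Outcomes are changes from week 0 to week 12. CIMT is the primary efficacy outcome.
- **Data analysis.** The FAS is everyone randomised who took at least one dose. Drop-outs, those lost to follow-up and those who stop medication are removed from the PPS. "Missing data will be used the last observation carried forward (LOCF) method".
- **Sample size.** Means 1.12 and 1.03 mm, SD 0.10, margin 0.03, one-sided α 0.025, power 0.8, minimum 90, and 114 after a 20% dropout allowance.

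**The concern.** The list merges three things that have different consequences for data: stopping study drug, deviating from the protocol, and leaving the study. Only the last makes a week-12 measurement unobtainable. A non-adherent or unblinded participant, or one with a gap in the record, can usually still attend at week 12, but the text asks such a person only for an undated last observation. Whatever is missing is then filled by LOCF.

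The reasons on the list relate to tolerability, adherence and events. The document gives no figures by arm, but these are the kinds of reason that can differ between an active and a placebo arm, so the missingness may be informative.

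The unblinding item also touches the endpoint outcomes. A non-fatal infarction, a stroke or a heart failure hospitalisation may lead to emergency unblinding, and unblinding makes the patient a drop-out. From then on, the patient's week-12 CIMT and any later event in the 12 weeks depend on a visit that is not required.

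**Working it through.** **Step 1. Reproduce the plan's sample size.** Inputs are from Sample size.

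- Effective difference: (1.12 − 1.03) − 0.03 = 0.06 mm. SD 0.10, one-sided α 0.025.
- Noncentrality with n per arm: 0.06 / (0.10 × √(2/n)).
- n = 44: power 79.5%. n = 45: noncentrality 2.846, power 80.4% (noncentral t). So 45 per arm, 90 in total, as stated.
- Dropout: 45 / 0.8 = 56.25, rounded up to 57 per arm, 114 in total, as stated.
- All 57 per arm with complete data: noncentrality 3.203, power 88.8%.

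The stated figures are correct. The 20% allowance replaces lost numbers; it does not allow for imputed values that pull the difference towards zero.

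**Step 2. Follow the rules for one participant.**

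| Event | Rule | Effect on data |
|---|---|---|
| Non-adherence or a data gap | Drop-out criteria | Drop-out; one undated last observation sought |
| Non-fatal infarction, stroke or heart failure hospitalisation | Endpoint outcomes | The event has occurred and can be counted with its date |
| Emergency unblinding for it | Blinding | Allocation revealed |
| Unblinded | Drop-out criteria | Drop-out; same undated last observation |
| No week-12 CIMT | Data analysis | Kept in FAS by LOCF; removed from PPS |

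One link is inferred. The article does not define a serious adverse event, but these three events are serious by the usual definition. Foot ulcer and stenosis progression need not be.

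**Step 3. Outer bound for the primary analysis.** Assumptions, none of which the article states: CIMT is measured only at weeks 0 and 12; a fraction d in each arm never returns and gets zero change by LOCF; completers change by 0 on placebo and by −0.09 mm on treatment; 0.10 is the SD of change.

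- Diluted effect against the margin: 0.09 × (1 − d) − 0.03. At d = 0.20: 0.072 − 0.03 = 0.042 mm.
- Shrunken SD, because imputed zeros have no spread. At d = 0.20, treatment variance is 0.8 × 0.01 + 0.2 × 0.8 × 0.09² = 0.009296 and placebo variance is 0.8 × 0.01 = 0.008. Their mean is 0.008648, SD 0.093.

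| d | Effect minus margin (mm) | Power, SD held at 0.10 | Power, SD shrunk |
|---|---|---|---|
| 0 | 0.060 | 88.8% | 88.8% |
| 5% | 0.0555 | 83.6% | 84.7% |
| 10% | 0.051 | 77.0% | 79.7% |
| 20% | 0.042 | 60.4% | 66.7% |

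The 10% row also describes 20% drop-out in which half return with a full-effect value.

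**Step 4. Size of the unblinding route.** The article gives no rate. If 0.5% to 5% of 114 were unblinded (assumed), that is 0.6 to 5.7 participants. Non-adherence and incomplete data are probably the larger source.

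**The case against.** **Drop-outs already stay in the analysis.** This stands. The FAS has no exclusion for drop-out, and these participants leave only the PPS. What is missing is the measurement, not membership of the set.

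**The last observation might be taken at week 12.** The wording allows it, so one cannot say that the value will be an early one. But it does not require it either, and an undated visit sought where possible does not secure the primary time point.

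**A reader might infer that cardiovascular endpoint events are themselves lost, or that every patient with one becomes a drop-out.** The documents do not support that. Unblinding is conditional on an emergency, the event precedes both the unblinding and the drop-out, and nothing in the text discards it or censors before it. Only what comes afterwards is at risk. The Discussion itself expects few such events in a short study.

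**A reader might also take 60% as the power that these rules produce.** It is not. That figure assigns the whole 20% to them, although ordinary loss and voluntary withdrawal are in the same allowance. It assumes that nobody returns, and it holds the SD at 0.10 while setting changes to exactly zero. Much of the harm in it comes from LOCF, which is a separate choice.

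**This belongs in the SAP.** Censoring detail may. Whether people are followed after stopping drug is a data-collection rule, and an SAP cannot recover measurements that were not taken.

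**Conclusion.** The point holds as a defect in data collection. As written, participants who could still be followed can lack a week-12 CIMT, and LOCF then supplies an earlier or baseline value. For patients unblinded after a non-fatal cardiovascular event, the triggering event can be counted, but later events and the week-12 CIMT are not secured; this route is likely to involve few of the 114.

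The size cannot be fixed from the article. The bound is about 60% to 67% power at 20% loss with no returns, against about 89% with complete data, under the assumptions in Step 3. The part due to non-adherence, incomplete data and unblinding is unknown and smaller. A difference in loss between arms is possible but not shown. The change is still worth making, because it is cheap and the article reports that recruitment is under way.

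**What to change.** Reconcile Drop-out criteria with Blinding, Endpoint outcomes and Data analysis:

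1. Divide the list into (a) discontinuation of study drug or protocol deviation and (b) withdrawal from the study. Limit (b) to withdrawn consent, death and true loss to follow-up.
2. State that unblinded, non-adherent or incomplete-data participants, who already remain in the FAS and leave only the PPS, attend the planned visits to week 12 for CIMT and endpoint events.
3. State that an endpoint event that leads to unblinding is counted, and that drop-out status alone is not a reason for censoring.

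No rule on when treatment stops is changed, and none is proposed. The cost is protocol wording and a few more week-12 visits in participants off study drug.
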